### Outcome assessment

Outcomes will all be assessed via a booklet of self-administered questionnaires that will be mailed to participants prior to the initial physical examination and at each of the follow-up points (5 weeks, 10 weeks, 26 weeks and 52 weeks post randomisation). Participants will return completed follow-up questionnaires to the researchers via mail marked only with their participant identification number. The outcomes to be measured in the trial are summarised in Table 3.

**Table 3 T3:** Outcome measures

Outcome measure	Measurement point (weeks)
**Primary outcome measures**	
1. Oswestry Disability Index V2.1 with "sex life" question replaced by a "work/housework" question	0, 5, 10, 26, 52
2. Numerical rating scale for back pain (0-10)	0, 5, 10, 26, 52
3. Numerical rating scale for leg pain (0-10)	0, 5, 10, 26, 52
**Secondary outcome measures**	
1. Global rating of change scale (7-point Likert scale)	5, 10, 26, 52
2. Satisfaction with physiotherapy treatment (5-point Likert scale)	5, 10, 26, 52
3. Satisfaction with *results *of physiotherapy treatment (5-point Likert scale)	5, 10, 26, 52
4. Number of work days missed in the last 30 days	0, 5, 10, 26, 52
5. Interference with work or housework in the past week (5-point Likert scale)	0, 5, 10, 26, 52
6. Quality of life (EuroQol-5D)	0, 5, 10, 26, 52
7. Orebro musculoskeletal pain questionnaire	0, 5, 10, 26, 52
8. Sciatica frequency scale	0, 5, 10, 26, 52
9. Sciatica bothersomeness scale	0, 5, 10, 26, 52

#### Primary outcome measures

Activity limitation will be evaluated using nine questions from the Oswestry Disability Index version 2.1 [64], with the tenth question relating to "sex life" being replaced by a question relating to "work/housework" [65,66]. Rasch analysis has shown that this modified version performs as well as the original Oswestry [65], but it is aimed at preventing missing responses to the "sex life" question. The Oswestry has been shown to be a reliable, valid and responsive instrument for measuring activity limitation in people with low back pain and referred leg pain [67-69].

Separate 0-10 numerical rating scales (NRS) will be used to measure the average intensity of back pain and leg pain over the past week, with end-point descriptors of "no pain" and "worst pain possible" [70,71]. The NRS has good reliability [72,73], responsiveness [74,75] and validity [76,77].

#### Secondary outcome measures

Global rating of change will be measured using a 7-point Likert scale, with participants rating their overall change since the baseline assessment as "completely recovered", "much improved", "slightly improved", "no change", "slightly worsened", "much worsened", or "vastly worsened" [78,79]. Various versions of this scale are considered to be reliable, responsive and valid [79,80].

In addition to global rating of change, participants will rate their satisfaction with physiotherapy treatment and their satisfaction with the results of physiotherapy treatment on separate 5-point Likert scales, with ratings from "very satisfied" to "very dissatisfied" [81-83]. These scales have good reliability, validity and responsiveness [84,85].

The Sciatica Frequency and Bothersomeness Scale will be used to assess the frequency and "bothersomeness" of a range of leg symptoms including leg pain, numbness or tingling, and weakness in the leg or foot [86]. This scale has been used in a number of trials, particularly those focussing on sciatica or disc herniation [56,87-89]. The scale is considered to be a specific quality of life measure and has compared favourably to the generic SF-36 in people with LBD [86]. It has been shown to be reliable [86,90], responsive, and valid [90,91].

Interference with work due to the LBD will be assessed in two ways. Firstly, at each assessment point participants will record the number of work days missed due to their back/leg condition over the previous 30 days [81,82]. Secondly, participants will rate the degree of interference with work (employment or housework) caused by their back/leg condition over the previous week on a five point scale ranging from "not at all" to "extremely" [81,82]. These measurement methods have demonstrated good reliability, validity and responsiveness [84,85].

The Orebro Musculoskeletal Pain Questionnaire will be used as a measure of psychosocial risk factors [92,93]. Although it is more commonly used as a prognostic screening tool at one point in time [94], in our trial the Orebro will also be administered at each follow-up point to detect changes in psychosocial risk factors over time. This appears justified given that the Orebro has good test-retest reliability and internal consistency [92,95], although its responsiveness as an outcome measure is unclear.

Health-related quality of life will be measured with the EuoQol-5D [96]. Utilities will be calculated according to the validated algorithms of Dolan [97]. The EuroQol-5D has good reliability, validity and responsiveness [98-100], is a recommended outcome measure for low back pain research [82] and has been used in several other low back pain trials [101-103].

### Adverse events

Adverse events will be measured in both groups using two methods. Firstly, physiotherapists will record any adverse events that occur during the treatment period on their standardised clinical notes for each participant, and these will be submitted to the researchers after four weeks, seven weeks and at the conclusion of the intervention period (ten weeks). In addition, an open question on all follow-up questionnaires will ask participants to describe any adverse, harmful or unpleasant effects that they attribute to the intervention.

### Participant compliance and co-interventions

The number of physiotherapy treatment sessions attended by each participant, and the number of missed or cancelled appointments, will be recorded by the treating physiotherapists. Participant compliance with their physiotherapist's advice and prescribed exercises will also be reviewed by physiotherapists at each visit via direct questioning and reviewing participants' exercise charts. Information regarding the nature and degree of co-interventions as well as medication usage will be obtained from participants on each follow-up outcome questionnaire.

### Data integrity

All questionnaire data will be scored and entered into a computer spreadsheet by a researcher blinded to the group allocation of the participant. Data will be checked for omissions and outliers to identify potential data entry errors and these will be clarified with the data enterer.

### Blinding

Given the nature of the interventions it will not be possible to blind participants or physiotherapists. However, all physiotherapists and participants will be informed that both treatment approaches are valid interventions that have a realistic chance of being beneficial and that neither approach is known to be more effective than the other. Physiotherapists will also be instructed to treat participants in both groups with the same degree of rigor, enthusiasm and optimism.

### Data analysis

Data analysis will focus on detecting the between-group treatment effect (with 95% confidence intervals) at each of the follow-up points (5 weeks, 10 weeks, 26 weeks and 52 weeks following randomisation). Analyses will be conducted using PASW Version 18^b^, with alpha set at 0.05 using a two-tailed hypothesis. Continuous data will be analysed using linear mixed models (with the group x time interaction estimating the treatment effect). These were chosen for their strength in analysing longitudinal biological data and accounting for correlations associated with repeated measurements [104-106]. The mixed models will adjust for the baseline score of the outcome of interest, along with the stratification variables (treatment centre and subgroup) as recommended by the revised CONSORT statement [107]. The inclusion of treatment centre as a random effect will account for the potential clustering of outcomes within treatment centres [108,109]. In addition, the mixed models will adjust for gender and Orebro Musculoskeletal Pain Questionnaire score, as gender and psychosocial factors are considered to be important prognostic factors [107]. Ordinal data will be analysed using the Mann Whitney U test.

At each follow-up point, participants in each group will be dichotomised according to whether they achieved the minimum clinically important difference of the outcome or not, and then the risk ratio, risk difference and number needed to treat will be calculated along with 95% confidence intervals [107,110]. Statistical significance will be evaluated using Chi square analysis. For these purposes, the minimum clinically important difference will be defined as 10/100 for the Oswestry [111], 2/10 for the NRS pain scales [111], at least "much improved" on the global rating of change scale [71,112] and "very satisfied" on the treatment satisfaction scales [71]. It has been argued that these values for minimum clinically important difference may be too low in some contexts [113], hence we will repeat this analysis using a threshold of 50% reduction in Oswestry scores and NRS pain scores based on empirical validation studies suggesting that this may be a more suitable threshold for important differences [67,114].

All data will be analysed on an intention to treat basis, in that all participants will be analysed in the treatment group to which they are initially allocated regardless of their compliance with that treatment [107,115]. All participants who withdraw from treatment for any reason will continue to be contacted for follow-up assessments and informed that their data are still required. Our primary method of analysis will not impute missing data [116]. This is justified as all methods of data imputation have limitations [107], and the linear mixed model analysis that we planned for analysing continuous data is thought to inherently account for missing data in a more effective and less biased manner than data imputation methods [105,106,117,118]. However, given the popularity of simple data imputation methods [105,107] we will undertake a secondary sensitivity analysis to determine whether the results would differ if missing data were replaced using the last observation carried forward method.

In addition to the analyses described above, subgroup analyses will be undertaken to estimate the effects of specific treatment on each of the five subgroups within the trial. This will be possible due to the stratification of the randomisation for subgroup which will ensure that each subgroup has a balanced allocation of participants between the specific treatment and advice groups. Preliminary analysis will need to be undertaken on two of the subgroups prior to the completion of the trial in order for PhD thesis submission deadlines to be met. It is often recommended that an alpha adjustment be made when interim analyses are to be performed [107,119]. However, in our trial the overall data from all trial participants will not be analysed prior to the completion of recruitment, so no adjustment in alpha will be made in the final analysis involving all participants.

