**Methods/Design:**

A multi-centre parallel group randomised controlled trial is proposed. A minimum of 250 participants with subacute (6 weeks to 6 months) low back pain and/or referred leg pain will be classified into one of five subgroups and then randomly allocated to receive either physiotherapy advice (2 sessions over 10 weeks) or specific physiotherapy treatment (10 sessions over 10 weeks) tailored according to the subgroup of the participant. Outcomes will be assessed at 5 weeks, 10 weeks, 6 months and 12 months following randomisation. Primary outcomes will be activity limitation measured with a modified Oswestry Disability Index as well as leg and back pain intensity measured on separate 0-10 Numerical Rating Scales. Secondary outcomes will include a 7-point global rating of change scale, satisfaction with physiotherapy treatment, satisfaction with treatment results, the Sciatica Frequency and Bothersomeness Scale, quality of life (EuroQol-5D), interference with work, and psychosocial risk factors (Orebro Musculoskeletal Pain Questionnaire). Adverse events and co-interventions will also be measured. Data will be analysed according to intention to treat principles, using linear mixed models for continuous outcomes, Mann Whitney U tests for ordinal outcomes, and Chi-square, risk ratios and risk differences for dichotomous outcomes.

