### Sample size

We will recruit a total sample size of at least 250 participants. We would require 128 participants (64 in each group) to detect the minimum clinically important difference between groups of 10% on the Oswestry assuming a standard deviation of 20 (two tailed hypothesis, alpha = 0.05, power = 80%) [120]. However, we wish to recruit more than this to improve power in our planned subgroup analyses. We acknowledge that the subgroup analyses are likely to remain underpowered [121], but they may provide some guidance for future research targeting the subgroups with greatest feasibility and effectiveness.

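### Three unranked primary outcomes at four visits, each at alpha 0.05, with no decisive test named: the stated 5% is not the error rate of the superiority claim

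*Protocol article*

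**What the plan says.** - **Outcomes.** The abstract of the protocol article states: "Primary outcomes will be activity limitation measured with a modified Oswestry Disability Index as well as leg and back pain intensity". Table 3 repeats the three as primary measures, all recorded at weeks 0, 5, 10, 26 and 52. Neither place ranks them.
- **Visits and alpha.** Under Data analysis, the between-group effect is sought "at each of the follow-up points (5 weeks, 10 weeks, 26 weeks and 52 weeks following randomisation", "with alpha set at 0.05 using a two-tailed hypothesis". No visit is singled out.
- **Model.** Continuous outcomes are analysed by "linear mixed models (with the group x time interaction estimating the treatment effect".
- **Responder analyses.** The same section dichotomises outcomes at each follow-up, tests them by chi-square, and repeats this for the Oswestry and pain scores at a 50% reduction. These analyses are not called primary.
- **Alpha adjustment.** The only discussion concerns interim analysis. It notes that two subgroups will be analysed before the trial ends, but that the full data will not be, "so no adjustment in alpha will be made in the final analysis involving all participants".
- **Sample size.** "We would require 128 participants (64 in each group) to detect the minimum clinically important difference between groups of 10% on the Oswestry", with SD 20, two-sided alpha 0.05 and 80% power. The recruitment target is at least 250.
- **Hypothesis.** The Discussion expects better clinical outcomes with specific treatment than with advice. It names no outcome or visit.

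**The concern.** Three outcomes at four visits give 12 mean comparisons, each at 0.05. The sample size describes one of them, and the protocol does not say which visit that one belongs to. Since nothing says which result decides the trial, superiority could be claimed on whichever comparison reaches significance, and the stated alpha would not be the error rate of that claim.

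Two features of the design make this matter more. Participants and physiotherapists are unblinded and every outcome is self-reported, so selective emphasis has little to check it. In addition, two subgroups are to be analysed early, so a lead outcome or visit chosen late could be chosen after some outcome data have been seen.

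**Working it through.** **1. The protocol's own figure.** Inputs from Sample size: difference 10, SD 20, two-sided alpha 0.05, power 80%.

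n per arm = 2 × (1.960 + 0.842)² × (20/10)² = 2 × 7.85 × 4 = 62.8, so 63 by the normal approximation. The two-sample t-test gives 63.8, so 64 per arm and 128 in total. The stated figure reproduces, for one test.

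**2. Number of tests.** 3 outcomes × 4 visits = 12. The responder tests are left out because they are not labelled primary.

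**3. Chance of at least one false significant result, all 12 null hypotheses true.**

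Independent tests: 1 − 0.95¹² = 46.0%.

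Correlated tests: 12 standard normal statistics were simulated (400,000 draws). Their correlation matrix was the product of a between-outcome and an exchangeable between-visit correlation. The documents give no correlations, so these values are assumptions.

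| Between outcomes / between visits | Either direction, any absolute z > 1.96 | Favouring specific treatment only, any z > 1.96 |
|---|---|---|
| 0.3 / 0.5 | 38% | 20% |
| 0.5 / 0.7 | 30% | 15% |
| 0.7 / 0.8 | 23% | 12% |
| 0.8 / 0.9 | 18% | 9% |
| Nominal, one test | 5% | 2.5% |

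If correlation instead decays with the gap between visits, the either-direction figures are slightly higher: 40.3% at 0.3/0.5 and 25.8% at 0.7/0.8.

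**4. The milder reading.** If group by time were one overall test per outcome, there would be three tests. Independent: 1 − 0.95³ = 14.3%. Treating them as three z-tests with correlation 0.7 gives 10.9%. The range is therefore about 11-14%.

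**5. What control costs.** Oswestry power by two-sample t-test, difference 10, SD 20. The 100 per arm column assumes 20% loss: 125 × 0.8 = 100.

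| Alpha | 125 per arm | 100 per arm |
|---|---|---|
| 0.05 | 97.6% | 94% |
| 0.05/3 = 0.0167 | 93.8% | 87% |
| 0.05/12 = 0.0042 | 85.4% | 74% |

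No SD is given for either pain scale, so the same calculation cannot be made for them.

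**The case against.** - **The success rule is inferred.** The protocol never says that one significant result out of 12 is enough, and it frames the aim as effects with 95% confidence intervals. This stands: the any-of-12 rate is conditional on a reading left open. The milder reading of one test per outcome fits less well with effects sought at each follow-up point, and it still gives 11-14%.
- **The 23-38% is not the chance of falsely declaring specific treatment superior.** A reader might infer that it is. It counts false results in both directions, while the stated hypothesis has one. The matching rate is about 12-20% against 2.5%. This stands.
- **The responder tests are not primary.** A reader might add two thresholds × 3 outcomes × 4 visits = 24 tests and speak of 36 primary tests. The protocol does not support that. It lists the scales themselves as primary, and it adds the 50% threshold as a repeat because the first may be too low. The responder analyses add unadjusted tests, but 12 is the count to defend.
- **There is a partial hierarchy.** The Oswestry is listed first and alone drives the sample size. This is a fair pointer to which outcome should lead, but it is not a stated rule, and it says nothing about the visit.
- **The details may sit in an analysis plan that is not shown.** This is true of an adjustment method. Which outcome and visit decide the trial is a protocol-level choice, and the article already fixes alpha, visits, model, covariates and its position on adjusting alpha.

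**Conclusion.** The concern holds in a bounded form. The protocol has three unranked primary outcomes, four visits at 0.05 each, no decisive test, and a sample size for a single Oswestry comparison at no stated visit. The interim-analysis argument against adjusting alpha does not address this.

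The size depends on two assumptions: that any one of the 12 comparisons could support the claim, and the correlations used. On those terms the either-direction error is about 23-38%, within a wider span of about 18-46%. Every reading examined exceeds the nominal level, including one overall test per outcome.

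The sample size arithmetic is correct. A reader might infer that 250 participants comfortably support adjustment across all 12 tests. The documents do not show this: Oswestry power at 0.05/12 falls from 85% to 74% under an assumed 20% loss, and power for the pain scales is unknown.

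**What to change.** Before any outcome data are analysed, including the preliminary analysis of two subgroups:

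1. Name the between-group Oswestry difference at one visit as the single confirmatory test at two-sided 0.05. Week 10, the end of both programmes, is one suitable choice. One visit must be fixed, and the sample size section should state it. This matches the existing calculation.
2. Only if that test succeeds, test back and leg pain NRS at the same visit with Holm: the smaller p-value against 0.025, then the other against 0.05.
3. Report all other visits and all responder analyses as supportive estimates with 95% confidence intervals.

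**Cost.** Protocol and registry wording. On the protocol's inputs the confirmatory Oswestry test has 97.6% power at 125 per arm and 94% at 100 per arm, so it needs no extra participants. The real price is that a significant pain result, or a result at another visit, can no longer carry the conclusion alone.

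Holm across all 12 comparisons is not recommended, because of the loss of power shown above.

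### The plan names the group x time interaction as the treatment effect in baseline-adjusted mixed models; read literally, this is not the adjusted group difference at each visit that the plan sets out to estimate

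*Protocol article*

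**What the plan says.** Three statements in the Data analysis section of the protocol article bear on this point.

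- The target: "Data analysis will focus on detecting the between-group treatment effect (with 95% confidence intervals) at each of the follow-up points", which the article lists as 5, 10, 26 and 52 weeks.
- The model term that carries the effect: "Continuous data will be analysed using linear mixed models (with the group x time interaction estimating the treatment effect".
- The adjustment: "The mixed models will adjust for the baseline score of the outcome of interest", together with the stratification variables, gender and the Orebro score.

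The rule applies to continuous outcomes, and so to all three primary outcomes: the modified Oswestry, back pain and leg pain. Table 3 has each of these measured at weeks 0, 5, 10, 26 and 52. The article does not say whether the week 0 score is also a response row in the model, or whether time is categorical.

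**The concern.** An interaction coefficient compares the group difference at one time with the group difference at a reference time. What it estimates therefore depends on which time is the reference, and that depends on whether week 0 is in the response.

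With baseline moved to the right-hand side, the usual meaning of adjusting for it, the reference is a follow-up visit at which treatment may already have worked. The interaction then omits whatever benefit is common to all visits. With week 0 kept as a response row, the reference is pre-treatment. The interaction is then a treatment effect, but not a baseline-adjusted one.

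This sentence names the estimator for every primary outcome. An analyst who follows it literally could report a lasting benefit as no effect, or report a less precise estimate than the plan promises. Because the readings give different primary results, the wording also leaves room to choose among them after the data are seen.

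**Working it through.** **Inputs.** From the Sample size section: a difference of 10 Oswestry points, SD 20, two-sided alpha 0.05, power 80%, at least 250 participants (taken as 125 per arm). From Table 3: weeks 0, 5, 10, 26 and 52. Assumed, because the article gives no figure: the same correlation rho between any two visits, 0.5 in the simulations and 0.3 to 0.7 in the formulas.

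**The plan's own figure.** The article states "We would require 128 participants (64 in each group"). The normal approximation gives 2 x (1.960 + 0.842)² x 20² / 10² = 62.8, so 63 per arm. The t-test version gives 63.8, so 64 per arm and 128 in total, an exact match. This calculation is for a group difference at one time point, not for an interaction.

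**Reading 1: follow-ups as response, baseline as covariate.** With week 5 as reference,

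E[Y at visit t] = a_t + b x baseline + g x group + d_t x group, with d_5 = 0.

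The effect at visit t is g + d_t; the interaction alone is d_t.

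- Constant benefit of 10 points: g = -10 and every d_t = 0.
- Benefit of 5, 7, 9 and 10 points at the four visits: the 52-week interaction is -10 - (-5) = -5, against a true effect of -10.

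Simulation of the constant 10-point benefit (60 trials of 250, rho 0.5, random participant intercept):

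| Quantity | Week 5 | Week 10 | Week 26 | Week 52 |
|---|---|---|---|---|
| Interaction coefficient | reference | 0.03 | 0.08 | 0.32 |
| Group plus interaction | -9.97 | -9.94 | -9.89 | -9.65 |

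The 0.32 is simulation noise: its between-trial SD is 2.474, and 2.474/√60 = 0.32. The joint interaction test rejected in 5% of trials, which is alpha. The visit-specific contrasts from the same fits were each significant in 98% to 100%. With time entered linearly, the group x week slope averaged 0.007 per week, against a truth of 0. The expected zero does not depend on rho.

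**Reading 2: week 0 also a response row, with the usual group main effect.** The interaction coefficients against week 0 averaged -10.06, -10.03, -9.98 and -9.74, so the benefit is recovered. Removing the baseline covariate left all four averages unchanged. The covariate is constant within a person, so with complete data it cancels from within-person change, and the estimate is the raw difference in change scores.

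Per-person variances:

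- change score: 2 x SD² x (1 - rho)
- baseline-adjusted: SD² x (1 - rho²)
- ratio: 2(1 - rho) / [(1 - rho)(1 + rho)] = 2/(1 + rho)

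| rho | Variance ratio | Equivalent share of sample lost, 1 - (1 + rho)/2 |
|---|---|---|
| 0.3 | 1.54 | 35% |
| 0.5 | 1.33 | 25% |
| 0.7 | 1.18 | 15% |

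Power under this reading at rho 0.5: the change-score SD is 20 x √(2 x 0.5) = 20, the SE is 20 x √(2/125) = 2.53, and 10/2.53 - 1.96 = 1.99, so power for 10 points is about 97% to 98%.

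**Reading 3: interaction as shorthand for the visit-specific contrasts.** This is the second row of the first table. It gives the baseline-adjusted difference at each visit, as the plan intends.

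The simulations left out centre, subgroup, gender and Orebro score; these do not change which term carries the effect.

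**The case against.** A reader might infer that the plan would estimate any constant benefit as zero. The document does not support that. The zero arises under one literal implementation only; week 0 as a response row, or visit-specific contrasts, both return about 10 points.

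The strongest defence is the section's own opening sentence, which asks for an effect with a confidence interval at each of four visits. Interaction coefficients from a follow-up-only model give three contrasts and none at the reference visit, and an overall interaction test gives no interval. So Reading 1 cannot produce the stated output, and the opening sentence can be taken as the key to the parenthesis. In a model coded without a separate group main effect, the group x time terms are exactly the visit-specific differences, and the phrase is common shorthand for that. Nowhere does the article say that an overall interaction test or a difference in slopes is the treatment effect. It can also be said that row structure and time coding are details an article leaves to the full plan.

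Much of this stands. It makes the zero conditional, and it makes Reading 3 the likely intention. Under Reading 2 the loss is one of precision only, and with 250 participants power for 10 points remains high at the assumed rho of 0.5. But the defence does not remove the point. The article does not merely leave the coding open; it states which term is the effect, and the sound reading requires replacing that term with another. Nothing else in the Data analysis or Sample size sections selects Reading 3 expressly.

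**Conclusion.** The point holds as an error in how the primary estimator is named, with consequences that depend on implementation.

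- Follow-up-only response, interaction coefficients or test reported as the effect: a constant benefit is estimated as zero, whatever the correlation, and a growing benefit is understated by its value at the reference visit.
- Week 0 as a response row: no bias under randomisation, but no baseline adjustment of the effect either. Variance is 1.54 to 1.18 times that of the adjusted estimate for an assumed rho of 0.3 to 0.7. The ratio assumes complete data and equal variances over time.
- Visit-specific contrasts: no problem.

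It would also be wrong to infer that the sample size is at fault. The 128 reproduces for a between-group difference at a single time point and is untouched by this.

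**What to change.** Replace the parenthesis about the interaction with a statement that:

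- the response is the set of four follow-up scores, with time categorical;
- the baseline score of the outcome is a covariate, alongside the other adjustments already listed;
- the treatment effect is the adjusted between-group difference at each visit (the group term plus the matching interaction term), with its 95% confidence interval.

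A baseline x time term may be added but is optional. The change is one sentence, made before analysis. It needs no new data, software or participants.
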